## 8.2 Baseline (Day 1): Evaluation and treatment procedures.

Patients who meet all inclusion/exclusion criteria at the screening visit will be asked to return to the clinic for the baseline visit (Day 1). Upon arrival, the following evaluations will be completed and recorded on the CRF by the study doctor:

- 8.2.1 Study I.D. number will be assigned by the pharmacist to the patient and placed on the CFR and consent form by the study doctor at each site .
- 8.2.2 Vital signs assessment. Patients with abnormal pulse rate, blood pressure or oral temperature  $>38^{\circ}\text{C}$  ( $100.4^{\circ}\text{F}$ ) or having acute illness on the day of the therapy must NOT receive the therapy. Temperature and acute illness must resolve within 7 days of initial scheduled visit in order to proceed with the study.
- 8.2.3 Limited physical exam, noting any changes from the screening examination. This must include any changes in the cutaneous lesion description obtained during the screening visit. Note: Do NOT proceed if patient has developed a mucosal lesion.
- 8.2.4 Female patients of childbearing potential must have a documented negative urine pregnancy test on day 1 of therapy and the date of the last menstrual period recorded.
- 8.2.5 Record any concomitant medications.

8.2.6 Make a drawing of each lesion using a plastic sheet, drawing the borders of each lesion on Day 1, and place in the CRF.

8.2.7 Photograph all cutaneous lesions using a digital camera with daylight (no flash) and with a distance of 15 cm from the center of lesions. A standard rule with a label of the ID patient code and date will be placed beside the lesion before taking the photograph. The pictures will be stored in a computer at IMTAvH sites and they will be accessed only by the study team.

Upon completion of these evaluations, the study doctor will review the inclusion/exclusion criteria for each patient. Patients who meet all eligibility criteria will have the following additional procedures completed on Day 1:

8.2.8 Provide the treatment (study nurse) as described in Section 7.

8.2.9 Monitor adverse events and cream application site reactions for 30 minutes post treatment and document on the CRF.

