## **6. Randomization, blinding and assignment of treatment.**

A randomization list from 1-80 will be generated by [name] at McGill University using a ratio of 1:1 to either the pentavalent antimony plus imiquimod arm or the pentavalent antimony plus placebo arm. The list will then be provided to a pharmacist, [name] at UPOCH who will be responsible for therapy preparation. This individual will not be involved in conducting the trials and therefore cannot administer the treatment or conduct patient evaluation(s). This list will contain the study I.D. numbers (1-80) and corresponding treatment assignments and remain completely blinded to the study investigators who will be treating and evaluating the patients.

Each patient will be assigned by the study doctor a study I.D. number from the above randomized list assigned in sequential order when he/she is enrolled in the trial. The study doctor at each site will ask to the study coordinator for the study ID number. The study ID number will be provide to the study coordinator by the pharmacist. This study ID number will be entered on the CRF for that patient. The nurse will then administer the treatment as detailed in section 7. The study doctor will carry out the evaluation and the nurse, doctor, and technician will remain blinded for the treatment and evaluation period.

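### The randomised study number is issued as the first Day 1 step, before the Day 1 checks and the eligibility review, so a patient who then fails permanently is already randomised

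*Protocol*

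**What the plan says.** **The number is the allocation.** Section 6 of the protocol says of the randomisation list: "This list will contain the study I.D. numbers (1-80) and corresponding treatment assignments". Numbers are "assigned in sequential order when he/she is enrolled in the trial". Section 7 places the randomised assignment on Day 1, and section 13 has each sealed package labelled with the study number.

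**The order of Day 1.** Section 8.2 lists the steps on arrival:

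- 8.2.1: "Study I.D. number will be assigned by the pharmacist to the patient".
- 8.2.2, vital signs and acute illness: a patient with an abnormal finding is not treated that day. "Temperature and acute illness must resolve within 7 days of initial scheduled visit in order to proceed with the study".
- 8.2.3, limited physical examination: "Do NOT proceed if patient has developed a mucosal lesion".
- 8.2.4, pregnancy: any female patient who could become pregnant "must have a documented negative urine pregnancy test on day 1 of therapy".
- 8.2.5 to 8.2.7: concomitant medications, lesion drawings and photographs. For the photographs, "A standard rule with a label of the ID patient code and date will be placed beside the lesion before taking the photograph".

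After these steps: "Upon completion of these evaluations, the study doctor will review the inclusion/exclusion criteria for each patient". Only patients who meet all criteria go on to treatment at 8.2.8.

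**The analysis sets.** Section 15 excludes patients with missing outcomes from the primary analyses. It adds an intention-to-treat analysis of everyone randomised.

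**The concern.** Randomisation should come after eligibility is settled and as close as practicable to the first dose. Here it precedes the checks that decide whether the patient may be treated at all. Screening may lie up to 30 days back (section 5), and the Day 1 checks are there because a patient's status can change in that time.

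A patient with a permanent Day 1 failure leaves two unattractive choices. Kept in the all-randomised set, that patient is ineligible and untreated, and dilutes the contrast between the arms. Removed, that patient is a post-randomisation exclusion and the effective sample is smaller. The list ends at 80, section 11 bars anyone who discontinues from re-enrolling, and the protocol has no rule for replacing or reissuing a number.

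**Working it through.** **Does any other section restore the right order?** Section 6 issues the number at enrolment, but the protocol never defines enrolment. Section 8.2 is the only step-by-step sequence. Its order is more than list numbering: the photograph at 8.2.7 already needs a patient code, and the eligibility review is expressly placed after all of these evaluations.

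**Which Day 1 failures cost a number?** Acute illness not resolved in the permitted 7 days, a new mucosal lesion, a positive pregnancy test, or another criterion found not to be met. Fever or acute illness that resolves in time costs nothing: the patient keeps the number and is treated later.

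**Inputs for the size.** From section 15: 40 per arm (80 in all), 80% power, log-rank test, 35% versus 67% cured, hazard ratio (HR) 2.6. Assumed: two-sided alpha of 0.05, since section 15 states neither alpha nor sidedness. Also assumed: k of the 80 numbers lost on Day 1, split evenly between arms, with k = 2 to 4.

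**Reproducing the plan's 80.** The HR implied by the two proportions is ln(0.33)/ln(0.65) = 1.1087/0.4308 = 2.574, and the mean cure proportion is (0.35 + 0.67)/2 = 0.51. Freedman's number of events is [(1.960 + 0.842)(HR + 1)/(HR − 1)]².

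- HR 2.6: 39.7, rounded up to 40 events; 40/0.51 = 78.4 patients.
- HR 2.574: 40.5, rounded up to 41 events; 41/0.51 = 80.4 patients.

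So Freedman's formula reproduces the plan's 80. Power at 80 patients (80 × 0.51 = 40.8 events) is Φ(√40.8 × 1.574/3.574 − 1.960) = Φ(0.853) = 0.803. With the rounded HR of 2.6 it is 0.810.

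**With k numbers lost (Freedman, from HR 2.574).** If these patients are dropped, events are (80 − k) × 0.51 and the HR is unchanged. If they are kept as not cured, both cure proportions are multiplied by (1 − k/80) and the HR is recomputed from the result.

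| k | Dropped: events | Dropped: power | Kept: cured, control / imiquimod | Kept: difference | Kept: power |
|---|---|---|---|---|---|
| 0 | 40.80 | 0.803 | 35.0% / 67.0% | 32.0 points | 0.803 |
| 2 | 39.78 | 0.793 | 34.1% / 65.3% | 31.2 points | 0.783 |
| 4 | 38.76 | 0.783 | 33.3% / 63.7% | 30.4 points | 0.762 |

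The difference column is 32 × (1 − k/80): 32 × 0.975 = 31.2 and 32 × 0.95 = 30.4.

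**Sensitivity to the formula.** Schoenfeld's power is Φ(½√events × ln HR − 1.960). At 80 patients it gives 0.855 (HR 2.574) or 0.863 (HR 2.6). With HR 2.574 and patients dropped it is 0.846 for k = 2 and 0.837 for k = 4. Kept as not cured, the recomputed HRs are 2.537 and 2.504, and power is 0.836 and 0.815. None of these falls below 80%.

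**The case against.** The strongest reply is that little may be lost in practice. Every Day 1 patient has met all criteria at screening within the previous 30 days, including a pregnancy test and a mucosal examination, so permanent failures may be rare. The 2 to 4 used above is an assumption without support in the protocol. The primary analysis drops patients with missing outcomes, so there the effect is a slightly smaller sample and not dilution. How randomised but untreated patients are classified may be settled in an analysis plan that is not shown. One could also read enrolment in section 6 as following confirmed eligibility.

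Most of this stands as a limit on size. It does not remove the defect: section 8.2 still puts the number first, and an undefined word in section 6 does not override an explicit sequence. An analysis plan could classify these patients but could not undo their randomisation.

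A reader might infer more than the protocol supports:

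- *Every patient stopped by a Day 1 check is never treated.* Section 8.2.2 lets a patient proceed once a temporary illness has resolved within 7 days.
- *The 40/40 and 20/20 split is broken.* Day 1 failures change how many are treated, not how many are allocated to each arm. The 20/20 per site in section 3 is not secured by the single list in section 6 in any case, because no stratification by site is described.
- *A Day 1 failure would be counted as cured at month 12.* That rule in section 15 is for patients lost to follow-up, in secondary analyses. Nothing extends it to someone found ineligible before treatment.
- *Selection bias.* The doctor making the Day 1 review is blinded to the allocation, so the review should not favour an arm.

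**Conclusion.** The concern holds as a defect of sequence: the protocol randomises before it confirms Day 1 eligibility, from a list with no spare numbers and no rule for reissue. The step order is clear from the text. The size of the consequence is not, because no Day 1 failure rate is given.

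On the assumed 2 to 4 lost numbers, power falls by 1 to 4 percentage points by Freedman's formula, and the planned 32-point difference shrinks by at most 1.6 points. The formula that reproduces the plan's 80 has almost no reserve, so with the implied HR of 2.574 even two lost numbers take power just under 80%. By Schoenfeld's formula it stays above. These figures rest on a two-sided 0.05 level and an even split between arms. The loss is modest, but it is avoidable, and the change also keeps the all-randomised set free of patients who were already ineligible for treatment on Day 1.

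**What to change.** 1. In section 8.2, move step 8.2.1 to after the inclusion/exclusion review, immediately before treatment at 8.2.8.
2. In section 6, define enrolment and state that the pharmacist releases a number only once Day 1 eligibility is confirmed and treatment can start. A patient with a temporary condition then receives a number when treatment can begin. No clinical criterion changes.
3. Introduce a separate screening code for the consent form, CRF, lesion drawings and photographs until the study number is issued, and record the link between the two. Without it, the photograph label at 8.2.7 and the Day 1 forms would have no identifier.

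The cost is a screening-code log and a later request to the pharmacist within the same visit. Section 7.2 opens the treatment package only when the cream is applied, so nothing in treatment depends on the number being issued earlier.

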### **8.3 Days 2-9 evaluation and treatment procedures**

8.3.1 Record any concomitant medications on the CRF.

8.3.2 Perform limited physical examination (study doctor).

8.3.3 Assess vital signs prior to treatment application.

8.3.4 Assess the active cutaneous lesions identified during the screening/baseline visits. Note presence and description of any additional lesions or mucosal lesions that may have appeared since the previous visit.

8.3.5 The study nurse will administer the treatment to the patient as described in Section 7 as long as there are no severe adverse events as detailed in section 10.1.

- 8.3.6 Monitor adverse events and injection site reactions for 30 minutes post treatment and document on the CRF.

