**7.1 Antimonial treatment:**

The total dose of pentavalent antimony (20 mg Glucantime™ /kg body weight/per day) for 20 consecutive days will be administered by intravenous with a syringe gauge # 23. Injections will be given by the nurse in alternating sites (i.e. veins in upper arms). Because a total of 20 injections will be administered during the course of the study, care must be taken to ensure that injections are not administered in the same exact location.

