#### **8.4 Day 10 evaluation and treatment procedures**

- 8.4.1 Record concomitant medications on the CRF.
- 8.4.2 Perform a complete physical examination (study doctor).
- 8.4.3 Assess vital signs prior to treatment application.
- 8.4.4 Assess the active cutaneous lesions identified during the screening/baseline visit. Note presence and description of any additional lesions that may have appeared since previous visit. Stop therapy if a mucosal lesion has developed
- 8.4.5 Record adverse events occurring since the last evaluation.
- 8.4.6 Take a drawing of each lesion using a plastic sheet, drawing the borders of each lesion.
- 8.4.7 Obtain photograph of the representative cutaneous lesion first photographed at baseline following the same procedures of section 8.2.7
- 8.4.8 Collect blood for safety evaluations as follows (study technician):  
Approximately 2.5 ml anticoagulated (EDTA) whole blood for CBC, white cell differential and platelet count.  
  
Approximately 8.5 ml whole blood into serum separator tube (SST) for serum chemistry testing. Chemistries to include: ALT, AST, total bilirubin, alkaline phosphatase, pancreatic amylase, glucose and creatinine.
- 8.4.9 Electrocardiogram: Only if a cardiovascular condition should be monitored.

- 8.4.10 Administer treatment to the patient as described in Section 7 as long as there are no severe adverse events as detailed in section 10.1 .

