#### **8.8 Safety and tolerability evaluation**

**8.8.1 Grading of side effects of the treatment at the at the cream application site (pain, pruritus, erythema and swelling):**

Grade 0 = none

Grade 1 = mild (easily tolerated)

Grade 2 = moderate (sufficiently discomforting to interfere with daily activities)

Grade 3 = severe (prevents normal daily activity)

**8.8.2 Grading of pain at the site of application site** will be according to the following definitions:

None

Mild (Some pain but does not limit the movement of the place where the lesion is located.)

Moderate (Limits movement)

Severe (Cannot move the place where the lesion is located)

**8.8.3 Grading of pruritus (itching) at the cream application site** will be made according to the following definitions:

None

Mild (Noticeable but easily tolerated)

Moderate (Sufficiently discomforting to slightly interfere with daily activities)

Severe (Constant discomfort. Leads to restriction of normal daily activities)

**8.8.4 Grading of erythema (inflammation) at the cream application site** will be according to the following:

None (0 to <1 cm in diameter)

Mild (1 to 4 cm in diameter)

Moderate (5 to 9 cm in diameter)

Severe (10 cm or greater in diameter)

**8.8.5 Grading of swelling at the cream application site** will be according to the following:

None

Mild (Some tenderness)

Moderate (Limits movement of the place where the lesion is located)

Severe (Cannot move the place where the lesion is located)

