#### Assessment of Intensity/Severity

The assessment of intensity/severity will be based on the investigator's clinical judgment and categorized as follows:

**Mild:** An adverse event which is easily tolerated by the patient, causing minimal discomfort and not interfering with daily activities.

**Moderate:** An adverse event, which is sufficiently discomforting to interfere with normal daily activities.

**Severe:** An adverse event, which prevents normal daily activities.

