#### Assessment of Causality

The investigator will use clinical judgment to determine the degree of certainty with which an adverse event is attributed to drug treatment. Alternative causes, such as natural history of the underlying diseases, concomitant therapy, etc are to be considered taking into account the known pharmacology of the drug, any previous reactions, literature reports and relationship to time of drug ingestion. Causality will be assessed using the following categories: not related, unlikely,

suspected (reasonable possibility) or probable. Patients with adverse events will be followed-up until the event disappears or the condition stabilizes.

If the treatment becomes intolerable to the patient for any reason (eg. Inflammatory response) this should be recorded as an AE and the cream application stopped.

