## **11. Patient Removal from Study**

Patients will be free to withdraw from the study at any time, for any reason, and without prejudice to further treatment. If the treating doctor determines that the clinical situation is worsening to an extent greater than a) one would expect from the natural history of the disease, or b) the range of clinical progression seen in previous cohorts of patients with similar initial clinical findings, he/she may elect to remove the patient from the clinical trial and to initiate treatment with the best medical regimen available.

Patients may also be removed from the study by the investigators, if necessary, in the event of a severe adverse event, pregnancy, or if the patient develops a concurrent illness which would preclude continuation in the study. Patients who are withdrawn from the study due to concurrent illness will be counseled by the investigators to receive the appropriate care. Patients who are removed from the study will undergo medical evaluations and will be followed for toxicity as closely as possible. Any patient who discontinues, regardless of the reason, will not be allowed to re-enroll in this study. The CRF will include reasons for withdrawal and any necessary treatment. Adverse events will be reported by the investigators and to the Ethics committee at UPOCH and McGill University.

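### A severe, intolerable cream-site reaction meets two dosing instructions, one withholding antimony and cream and one stopping only the cream, with no stated precedence or duration; erythema is also graded on two incompatible scales

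*Protocol*

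**What the plan says.** **Dosing condition.** For Days 2-9, Protocol 8.3.5 has the nurse "administer the treatment to the patient as described in Section 7 as long as there are no severe adverse events", with a reference to 10.1. Day 10 (8.4.10) repeats it: "Administer treatment to the patient as described in Section 7 as long as there are no severe adverse events as detailed in section 10.1". Sections 8.5.5 (Days 11-19) and 8.6.8 (Day 20) carry the same condition.

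**What Section 7 contains.** Section 7.1 is the antimony: "The total dose of pentavalent antimony (20 mg Glucantime™ /kg body weight/per day) for 20 consecutive days". Section 7.2 is the imiquimod or placebo cream, nine applications over the same period.

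**Cream rule inside 10.1.** Under Assessment of Causality, if treatment becomes intolerable, with an inflammatory response as the example, "this should be recorded as an AE and the cream application stopped". Antimony is not mentioned.

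**Removal.** Section 11: "Patients may also be removed from the study by the investigators, if necessary, in the event of a severe adverse event".

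**Grading.** The intensity scale in 10.1 defines severe as "An adverse event, which prevents normal daily activities". Section 8.8.1 uses the same kind of functional criterion for pain, pruritus, erythema and swelling at the application site. Section 8.8.4 then grades erythema by size alone: "Severe (10 cm or greater in diameter". Sections 8.8.2 and 8.8.5 grade severe pain and swelling by loss of movement.

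**The concern.** The objective is to compare antimony plus imiquimod with antimony alone, so antimony should be given on the same terms in both arms. Read literally, the dosing condition withholds the antimony as well as the cream when a cream-site reaction is severe. The instruction in 10.1 stops the cream and is silent on antimony. Staff facing one reaction can therefore follow the protocol and still treat the patient in two different ways.

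If the literal reading is followed and cream reactions are more frequent on active cream, the treatment contrast mixes the added effect of imiquimod with a loss of antimony. The analysis set can be affected too. Section 11 provides toxicity follow-up for removed patients but states no efficacy follow-up, and Section 15 excludes patients with missing outcomes from the primary analyses.

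The two erythema scales are a separate defect. The frequency of severe erythema, a tolerability result, depends on which subsection the assessor used.

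**Working it through.** **1. The two rules side by side**

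| | 8.3.5, 8.4.10, 8.5.5, 8.6.8 | 10.1, Assessment of Causality |
|---|---|---|
| Trigger | Severe adverse event, per 10.1 | Treatment intolerable for any reason |
| What is withheld | Everything in Section 7 (antimony and cream) | Cream |
| Duration | Not stated | Cream stopped; antimony not addressed |
| Precedence | Not stated | Not stated |

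The triggers differ, so the rules collide only for an event that meets both. A severe, intolerable inflammatory reaction to the cream does.

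**2. What the missing duration means for antimony exposure**

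The course is 20 daily doses. One withheld day leaves 19/20 = 95%. A permanent stop from Day 6 leaves 5/20 = 25%. The text allows either.

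**3. The plan's own power figure**

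Inputs from Section 15: 40 per arm, 35% and 67% cured, hazard ratio 2.6, log-rank test, 80% power. Alpha is not stated; 0.05 two-sided is assumed.

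- Hazard ratio = ln(1 − 0.67)/ln(1 − 0.35) = 2.57, given as 2.6.
- Expected cures = 40 × (0.35 + 0.67) = 40.8.
- Freedman power = Φ(√40.8 × (2.57 − 1)/(2.57 + 1) − 1.96) = 80.3%; with 2.6 it is 81.0%.

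The stated 80% reproduces. This point does not rest on a sample-size error.

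**4. Illustration of unequal antimony loss**

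Assume a share f of the 40 imiquimod patients loses antimony and is cured at rate q instead of 67%, with controls unchanged at 35%. Then the experimental cure proportion = 0.67(1 − f) + qf, and the loss = f × (0.67 − q). Neither f nor q comes from the documents. Entries are loss in percentage points, then Freedman power.

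| q | f = 5% (2 patients) | f = 10% (4) | f = 20% (8) |
|---|---|---|---|
| 0 | 3.4; 71.6% | 6.7; 61.3% | 13.4; 38.8% |
| 0.35 | 1.6; 76.4% | 3.2; 72.0% | 6.4; 62.3% |
| 0.50 | 0.9; 78.3% | 1.7; 76.1% | 3.4; 71.4% |

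The q = 0 row is an extreme. The table also assumes that these patients would have cured at 67% had antimony continued. If stopping the cream alone lowers their cure rate, less of the loss is due to antimony.

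**5. The erythema scales**

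Redness of 10 cm or more that does not limit activity is severe under 8.8.4 but not under 8.8.1 or 10.1. Redness below 10 cm that prevents activity is the reverse. Lesion size alone moves the 8.8.4 grade. A circular lesion at the 25 cm² limit in 4.2 has diameter 2√(25/π) = 5.6 cm, or 5.6 + 2 × 0.5 = 6.6 cm with the treated margin in 7.2. Redness confined to the treated area would already be moderate by diameter, whatever its effect on the patient.

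**The case against.** The best defence is that the dosing rule cites 10.1, and 10.1 contains the cream instruction. A site could read the specific sentence as governing cream reactions and the general condition as governing other severe events. That is reasonable, but the protocol does not say so, and the specific sentence applies to intolerability for any reason, not only to cream reactions. The gap in precedence and duration stands.

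The defence succeeds against several stronger readings that a reader might draw:

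- **Three conflicting actions.** Removal under Section 11 is discretionary and compatible with either dosing rule. It is a further, unranked option and not a contradiction.
- **Painless erythema of 10 cm stops antimony.** The dosing rule names the scale in 10.1, which agrees with 8.8.1. The diameter scale reaches dosing only if staff carry an 8.8 grade across.
- **The course ends.** The conditions in Section 8 apply to each treatment day. Nothing says that one withheld dose ends the course.
- **The loss falls mainly on the imiquimod arm.** This is an inference. Only the cream differs between arms, but no reaction rates are given, and severe antimony toxicity could trigger the same condition in both arms.
- **Lima and Cusco will diverge.** This is possible, but the protocol describes common training and oversight, and Section 15 specifies no test between sites.

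Some safeguards already exist. Drug administration, changes to the dosage schedule and reasons for withdrawal go on the CRF, and an intention-to-treat analysis of all randomized patients is planned. These document the problem and limit selection, but they do not restore antimony exposure or tell staff which rule to follow.

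**Conclusion.** The point holds in a limited form. For a cream-site reaction that is both severe and intolerable, the protocol gives two instructions with different consequences for antimony, without precedence or duration. This is more than missing detail, because the Section 8 rule taken literally withholds the drug common to both arms for a reaction to the cream, the only component that differs.

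The size is unknown. The loss of 0.9 to 13.4 points, against the planned 32-point difference, and the matching power of 78.3% down to 38.8% rest wholly on assumed shares of 5-20% in one arm, none in the other, and assumed cure rates of 0-50%. They show that the plan has little slack and do not predict a loss.

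The conflict between 8.8.1 and 8.8.4 is certain on the text, but it bears on tolerability reporting and not formally on dosing.

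**What to change.** Amend the protocol so that:

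1. 8.3.5, 8.4.10, 8.5.5, 8.6.8, the cream instruction in 10.1 and Section 11 are reconciled into one rule, cited identically in each place. It should state which component (cream, antimony or both) is withheld and for how long, and separate stopping a component from leaving the study.
2. One scale is named for grading cream-site erythema, and the scale that governs the dosing rule is stated explicitly, whether that in 10.1 or another the sponsor chooses.
3. The CRF records the stop date and reason separately for cream and for antimony.

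Which clinical rule applies is for the sponsor and investigators to decide. The cost is a short amendment and a few CRF fields, with no added visits or patients.
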